**2**.**4 Speculum lubrication and adequacy of cervical smears**

The practice of speculum lubrication for vaginal examination is varied due to the fears that lubricants can alter the adequacy of cytological smears. However, recent studies have investigated the relationship between speculum lubrication and Pap smear accuracy and showed evidence supporting that speculum lubrication does not disrupt the evaluation of cytological smears.

Amies et al^33^ in their study randomized five public health family planning clinics in USA to lubricating gel and water arms. A sum of 2906 Pap smear specimens were obtained, 1440 from units using lubricants and 1466 from the non-lubricant using clinics. A dime size of the lubrication gel was stated to have been applied on the external part of the inferior blade of the plastic disposable speculum which is not objective as this might be difficult to ascertain by different people because a dime is not a standard way of measurement. Inadequate smear rate for the clinics using lubricant compared to clinics not using lubricants was 1.4% versus 1.3%. The percentage of inadequate smears for the clinics using gel did not differ significantly from those of the control clinics [Odds ratio (OR) 1.1; 95% Confidence Interval (CI) 0.6, 2.0]. Reasons for unsatisfactory smears were scanty cells, excess blood and inflammation. Drying artefact or gel overlay was not encountered as causes of encumbrance in evaluation. They did not evaluate the pain level during speculum insertion.^33^

In 2012, Uygur et al ^20^ demonstrated in Turkey that speculum lubrication did not alter cervical cytological smears. A total of 400 eligible women were grouped at random into two arms: the gel and no gel groups. Each arm was then subsequently randomly divided to have liquid based smears or conventional smears. Dime sized gel was spread on the outer side of the lower blade as done by Amies et al which is not a standard way of measurement and will not be easily reproducible. Out of the 400 women only 3 unsatisfactory results were recorded, one from the group that did not use gel( 0.5%) and two from the other group(1%).^20^

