**CHAPTER FOUR**

**RESEARCH METHODOLOGY**

4.**1 STUDY DESIGN**

The work will be a randomized controlled study.

4.2 **STUDY SETTING**

This work will be done in the gynaecology clinic of Nnamdi Azikiwe University Teaching Hospital (NAUTH) Nnewi, Anambra State Nigeria. NAUTH is the only federal teaching hospital in Anambra State, a state in the South eastern part of the country. It offers comprehensive and tertiary services to occupants of Anambra, Enugu, Delta, Imo and Abia states. It is structured to offer medical undergraduate and medical postgraduate training as well as paramedical training. It is also well grounded in medical research. This teaching hospital is well equipped to offer obstetric, gynaecological and gynae-oncology services both on in-patient and outpatient bases. Nnewi is one of the biggest towns in Anambra state and consists of 4 villages which include Nnewichi, Uruagu, Umudim, and Otolo. ^41^ It is a place known for its industrial and commercial activities. It is home to the popular Nkwo Nnewi market, the biggest market for motorcycle spare parts in West Africa.^41^ It is home also to major automobile, petrochemical and cosmetic industries and the first indigenous car producing plant in Nigeria. The inhabitants are mainly Christians who speak Igbo majorly and are mostly traders.

4.**3 SAMPLE SIZE DETERMINATIONf**

The sample size will be calculated using the formula for sample size Determination of minimum sample size for experiemtal studies (Difference in proportions) ^42^ substituting for the values of proportion of unsatisfactory smears as found in a previous study ^20^

n **=** [(Z**_β_** + Z**_α/2_**)^2^ x 2P(1−P)] **=** Minimum sample size

E ^2^

Where

P **=** (P_1_ + P_2_) / 2 **=** (0.01+ 0.005) / 2 **=** 0.0075

E **=** Effect size **=** P_1_ - P_2_ **=** 0.01- 0.005 **=** 0.005

Z**_β_ =** Corresponding Z value at 80% Power **=** 0.84

Z**_α/2_** **=** Corresponding Z value at 95% confidence level **=** 1.96

n **=** [(0.84 + 1.96)^2^ x 2(0.0075)(0.9925)] **=** 0.116718 **=** 4668.72 **≈** 4669

(0.005) ^2^  (0.005) ^2^

Adjusting for finite population, N = 60 samples from clinic in 3 months.

n_s_ **=** n^1^ / 1 + n^1^/N

Where;

n_s_ **=** Adjusted sample size

n^1^ **=** Calculated sample size

N **=** population for study

n_s_ **=** 4669 / (1 + 4669/60) = 4669/78.82 = 59.2 **≈** 60

This will be approximately 60 making a total of 120 with 60 controls and the other 60 for intervention arm.

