However, considering attrition rate of 10.0% will give 6 subjects, there will be 6 women in each of intervention and control groups. Therefore, the total number of subjects in each arm = 60 + 6 = 66. So a total of 132 subjects will be recruited for the study.

4.4 **ETHICAL CONSIDERATIONS**

Ethical approval will be gotten from the Ethics Committee of Nnamdi Azikiwe University Teaching Hospital Nnewi before embarking on the study. An informed consent will be gotten from patients before they are selected to participate in the research. The women will choose to take part in the research or withdraw at any time and will be assured of getting standard quality of care without prejudice. The researcher will fund the research and none of the participants will pay for the procedure or investigation. There will be minimal discomfort to the participants. The research assistants and participants will not be given incentives. Information gathered from this study will be treated as strictly confidential.

4.5 **STUDY POPULATION**

The women will be recruited from consenting patients who are at least 25years old who present to the gynaecological clinic of NAUTH Nnewi for routine Pap smear.

4.6 **INCLUSION CRITERIA**

The participants will include pre and post-menopausal women who require Pap smear.

4.7 **EXCLUSION CRITERIA**

The following women would be excluded from the work virgins, pregnant women, women having their menstrual period, women with any overt cervical pathology, women with vulvar pathologies or those on hormone replacement therapy. Women with vaginitis, those undergoing vulvectomy or vaginectomy and women who had fertility-sparing surgery will not be recruited.

4.8 **DATA COLLECTION**

Training will be organized for five Senior Registrars who will work as research assistants. The researcher and the 5 trained research assistants will collect data from the participants at the gynaecological clinic with the aid of a proforma. NAUTH runs outpatient services on every working day and emergency services for 24 hours every day. On the average 2 smears are collected each day for cervical cancer screening in the gynaecological clinic making 10 in a week and 40 samples in a month. So it is expected that the sample size of 102 will be achieved in 3 months.

4.**9 SAMPLING APPROACH, RANDOMIZATION AND ALLOCATION SEQUENCE**

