The vial will then be taken to the histopathology laboratory of Nnamdi Azikiwe University Teaching Hospital, Nnewi where it would be transferred into a centrifuge tube with same quantity of cleaning solution. The fluid will then be centrifuged for 10 minutes at 1400 rpm; the supernatant will be removed. Smears will be made from the sediments after mixing with the cellular base solution (Diapath S.p.A Martinego, Italy) and stained by the Papanicolaou staining method and reported using the Bethesda system stating whether the sample is satisfactory or not and the reason for unsatisfactory results. Samples will be recorded as “unsatisfactory” if no endocervical cells are present, if they are obscured by blood, or if drying artifact or gel overlay are present; otherwise, they will be recorded as “satisfactory”. ^19^ The histopathologist will not be aware of the intervention arm (group of patients) to which the smears to be analysed belong.

4.11 **OUTCOME MEASURES**

The primary outcome measures will be the mean NRS pain scores and proportion of women with inadequate cervical cytology smears while the secondary outcome measures will be the pattern of Pap smear results and proportion of women willing to come for repeat testing.

4.12 **PLANNED HANDLING OF RESULTS**

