4.12.1 DATA AND STATISTICAL ANALYSIS

Statistical Packages for Social Sciences (SPSS) version 25 would be employed in the analysis of results. Charts and tables would be used to represent collected data. Means and standard deviations will be used to represent continuous data. T-test would aid the assessment of parametric variables and Mann Whitney U-test would be used for non-parametric ones. Statistical test of significance would be deduced at p-value less 0.05.

DUMMY TABLE 1 SOCIO-DEMOGRAPHIC AND CLINICAL CHARACTERISTICS OF THE STUDY POPULATION

| CHARACTERISTIC | ALL | GEL GROUP | NON GEL- GROUP | P-VALUE |
| --- | --- | --- | --- | --- |
| AGE: (years)  25-30  31-40  41-50  Above 50 |  |  |  |  |
| PARITY:  P0  P1  P2-4  P>5 |  |  |  |  |
| MARITAL STATUS  Single  Married  Divorced  Widowed |  |  |  |  |
| MENOPAUSAL STATUS:  Pre-menopausal  Post-menopausal |  |  |  |  |
| USE OF HORMONAL DRUGS OR DEVICES:  Positive history  Negative history |  |  |  |  |

TABLE 2. PAP SMEAR SAMPLE ADEQUACY

| **Laboratory Findings** | **All** | **Gel** | **No gel** | **P-value** |
| --- | --- | --- | --- | --- |
| Satisfactory Pap smear sample |  |  |  |  |
| Unsatisfactory Pap smear sample |  |  |  |  |

TABLE 3. PAP SMEAR RESULT PATTERNS

| Pap smear results | All | Gel | No gel |
| --- | --- | --- | --- |
| HSIL |  |  |  |
| LSIL |  |  |  |
| ASC-US |  |  |  |
| ASC –H |  |  |  |
| BCC |  |  |  |
| WITHIN NORMAL LIMITS |  |  |  |

**List of abbreviations:** HSIL-High Grade Squamous Intraepithelial Lesion, LSIL- Low Grade Squamous Intraepithelial Lesion, ASC-US- Atypical Squamous Cells of Undetermined Significance. ASC-H- Atypical Squamous Cells in which a High-Grade Squamous Intraepithelial Lesion (HSIL) cannot be excluded, BCC-Benign Cellular Changes.

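### A finite-population correction cuts 4,669 women per arm to 60, which leaves almost no power for the smear-adequacy difference used in the calculation; the pain outcome has no sample-size basis

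*Protocol*

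**What the plan says.** Section 4.3 sizes the trial on the proportion of unsatisfactory smears alone. It uses the two-proportion formula with 1.0% (gel) and 0.5% (no gel), the rates reported in section 2.4 for a 400-woman trial (reference 20). The normal deviates are 0.84, labelled "Corresponding Z value at 80% Power", and 1.96, labelled "Corresponding Z value at 95% confidence level". The result is 4,669.

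The next step reads "Adjusting for finite population, N = 60 samples from clinic in 3 months". It applies n/(1 + n/N), obtains 59.2, and concludes: "This will be approximately 60 making a total of 120 with 60 controls and the other 60 for intervention arm". Adding 10% for attrition gives 66 per arm, 132 in all.

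Section 4.8 describes the clinic's throughput as "making 10 in a week and 40 samples in a month".

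Section 4.11 names two primary outcomes: "The primary outcome measures will be the mean NRS pain scores and proportion of women with inadequate cervical cytology smears". Section 4.12.1 sets the significance level: "Statistical test of significance would be deduced at p-value less 0.05". No difference, standard deviation or power for pain is stated anywhere.

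**The concern.** The finite-population correction belongs to surveys. It reduces the sample needed to estimate a quantity in a fixed, closed population when much of that population will be sampled. A randomised comparison has a different aim. Its power depends on the number of women in each arm and on the event rates, not on how many women pass through the clinic in three months. Moreover, n/(1 + n/N) can never exceed N, whatever effect or power is entered. When n is far larger than N, it returns roughly N. The figure of 60 is therefore the clinic count, and the 80% power input no longer has any bearing on it.

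The step also fails on its own terms. It draws 60 women for each of two arms, 120 in total, from a stated population of 60. That population also disagrees with the throughput in section 4.8.

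Adequacy is a stated aim, objective and hypothesis, and the introduction gives worry about interference with cytology as the reason lubrication is discouraged. A non-significant adequacy result is close to certain at this size even if the assumed difference is real. A reader who sees 80% power in the calculation could take such a result as reassurance.

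**Working it through.** **Inputs.** From section 4.3: p1 = 0.01, p2 = 0.005, mean P = 0.0075, E = 0.005, deviates 0.84 and 1.96, N = 60. From section 4.8: 40 samples a month.

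**1. The plan's own figure.**
n = (0.84 + 1.96)² × 2 × 0.0075 × 0.9925 / 0.005² = 0.116718 / 0.000025 = 4668.72, so 4,669. This reproduces. It is a per-arm figure, because the formula carries 2P(1 − P) and the corrected value is assigned to each arm. Without the correction the total would be 2 × 4,669 = 9,338.

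**2. The correction.**
4669 / (1 + 4669/60) = 4669 / 78.82 = 59.2, taken as 60. This also reproduces. The arithmetic is right; the method does not apply.

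**3. Sensitivity to N.**
Section 4.8 implies 3 × 40 = 120 samples in three months. The same formula gives 4669 / (1 + 4669/120) = 117 per arm. The answer follows whichever clinic count is entered.

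**4. Power at 60 per arm, 1.0% against 0.5%.**
- Normal approximation: standard error = √(2 × 0.0075 × 0.9925 / 60) = 0.01575. The standardised difference is 0.005 / 0.01575 = 0.317. The tail in the assumed direction is Φ(0.317 − 1.96) = 5.0%. The opposite tail is Φ(−0.317 − 1.96) = 1.1%. Together they give about 6.1% (6.2% before rounding).
- Uncorrected chi-square, by enumerating the two binomial distributions: 0.24%.
- Fisher's exact test, by the same enumeration: 0.002%.

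If all 66 per arm are evaluable, the last two become 0.33% and 0.004%. With no event in one arm, Fisher's test needs 6 in the other for p < 0.05 (p = 0.027); 5 against 0 gives p = 0.057.

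**5. Events expected at those rates.**
60 × 0.01 + 60 × 0.005 = 0.9 in the whole trial. The chance of none in either arm is 0.99⁶⁰ × 0.995⁶⁰ = 0.547 × 0.740 = 0.405, about 41%.

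**6. What 60 per arm delivers for pain.**
The protocol fixes no SD, so one must be assumed. Section 2.5 gives SDs of 1.57 and 1.71 at speculum introduction in a gel-against-water trial, and √((1.57² + 1.71²)/2) = 1.64. Section 2.5 also gives means of 2.3 and 1.6 in the trial that supplied the smear rates, a difference of 0.7. With a two-sided 5% t-test:

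| Assumed SD | Difference detectable with 80% power | Power for 0.7 points |
|---|---|---|
| 1.2 | 0.62 | 89% |
| 1.64 | 0.85 | 64% |
| 2.0 | 1.03 | 48% |
| 2.5 | 1.29 | 33% |

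**The case against.** Several things can fairly be said for the plan.

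- **It hides nothing.** The 4,669 is printed, and the protocol never states the power at 60 per arm. A reader might infer that it expressly claims 80% power for 60 women per arm, or that the result will be published on that footing. The text supports neither. What stands is that 60 is presented as the outcome of a calculation whose power input no longer applies.
- **60 per arm is not hopeless for every contrast.** A reader might infer that the trial would miss even the most extreme effects in the literature review. It would not: 26.9% against 1.2%, quoted in section 2.3 for carbomer-containing gels, has 99% power by Fisher's test. For 12.1% against 1.7%, quoted in section 2.4, power is 47% by Fisher and 66% by uncorrected chi-square. Neither comes from a comparable design. The first is retrospective and was seen mostly in vaginal smears; the second is from paired smears with gel placed on the cervix itself. They do not bear on power for the difference the plan chose.
- **The event rate may differ.** Section 4.10 also counts a smear as unsatisfactory when endocervical cells are absent. If the source trial did not, rates here could differ. The 0.9 events and the 41% are therefore conditional on 1.0% and 0.5%, but those are the rates on which the plan rests its calculation.
- **Pain may be adequately served.** Being unsized is not the same as being underpowered. Over the assumed SDs, power for 0.7 points runs from 33% to 89%, so the documents do not show that 60 per arm is too few.

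**Conclusion.** The sample-size justification for adequacy does not hold and must be corrected. The formula gives 4,669 per arm; the reduction to 60 comes from a correction that has no place in a two-arm comparison. At the plan's own rates, power falls from 80% to about 5% to 6% by normal approximation, and to well under 1% by the enumerated tests. This conclusion does not depend on the choice of test or on whether 60 or 66 per arm are evaluable. It does depend on the assumed 1.0% and 0.5%.

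The second part also holds: one of the two primary outcomes has no sample-size basis. The pain figures rest on an assumed SD taken from a visual analogue scale at speculum introduction, gel against water, in gynae-oncology patients. This trial takes one numeric rating at the end of the procedure, gel against a dry speculum. The figures are indicative only.

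A reader might infer that pain must become the sole primary outcome. The documents do not require that: adequacy is a stated aim, objective and hypothesis, and keeping two primary outcomes is a design choice open to the sponsor.

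**What to change.** In section 4.3:

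1. Delete the finite-population step and the 80% power basis for adequacy.
2. State that 4,669 per arm would be needed for 1.0% against 0.5%, and that 60 evaluable per arm has negligible power for that difference.
3. Keep 132 women and state what 60 per arm delivers for pain, with the SD marked as an assumption and its origin disclosed. At SD 1.64 this is 80% power for 0.85 points and 64% for the 0.7 points seen in the source trial. Over SD 1.2 to 2.5, the difference detectable with 80% power runs from 0.62 to 1.29. The 0.85 is what this sample size happens to detect, so 0.7 should be shown beside it.

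In section 4.12.1, say that adequacy will be reported as a difference in proportions with a confidence interval, and that a non-significant result will not be read as evidence of no effect.

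Reconcile the 60 samples in three months in section 4.3 with the 40 a month in section 4.8.

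Naming pain as the single primary outcome, with matching changes to section 4.11 and the abstract, is an option for the sponsor and not part of the required correction.

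The cost is rewording, with no additional women. The price is candour: the stated power for adequacy becomes much less favourable.

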**ABSTRACT**

**Background:** Carcinoma of the cervix is the most prevalent gynaecological malignancy in our environment, and it is associated with significant morbidity and mortality. Papanicolaou test is a well-recognised and efficient screening modality but the uptake of Pap smear in our environment remains poor. Fear of pain from speculum insertion during vaginal examination has been noted as a factor that may reduce the compliance of women to cervical cancer screening and repeat testing. Speculum lubrication may help to reduce these pain and discomfort, but there are fears of its interference with cytological results.

**Aim and Objectives:** To determine and compare adequacy of cervical cytology smears and mean pain scores of women undergoing cervical screening with or without speculum lubrication.

**Research Methodology:** This proposed work will be a randomized controlled study among women having cervical cancer screening at the gynaecological clinic of Nnamdi Azikiwe University Teaching Hospital, Nnewi. Sixty-six patients would be randomly assigned to the ‘Gel group’ and another 66 patients to the ‘No Gel’ group. Samples will be collected from each participant for Pap smear with lubricated vaginal speculum for the ‘Gel group’ and non-lubricated vaginal speculum for the ‘No Gel group’. Pain scores will be assessed with the numeric rating scale for pain. The primary outcome measures will be the mean numeric rating scale pain scores and proportion of women with inadequate cervical cytology smears.

**Handling of Results:** The Statistical Packages for Social Sciences (SPSS) would be employed for data analysis. Statistical test of significance would be deduced at p-value less than 0.05.

**Strengths and Limitations: T**his proposed study is the first of its kind in Nigeria. Conclusions may not be generalized to other types of lubricant gels since only one type of lubricant gel will be used. The histopathologist and the study participants will be blinded hence double-blind.

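### Section 4.8 of the protocol gives a sample size of 102 in 3 months where section 4.3 and the abstract set 132, and the two sections use clinic volumes that differ by a factor of two

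*Protocol*

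**What the plan says.** **Target.** Section 4.3 arrives at 60 per arm: "This will be approximately 60 making a total of 120 with 60 controls and the other 60 for intervention arm". It then adds an allowance for loss ("considering attrition rate of 10.0% will give 6 subjects" per arm) and concludes: "So a total of 132 subjects will be recruited for the study". The abstract agrees: "Sixty-six patients would be randomly assigned to the ‘Gel group’ and another 66 patients to the ‘No Gel’ group". Section 4.8 gives a different number: "So it is expected that the sample size of 102 will be achieved in 3 months".

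**Clinic volume.** Section 4.3 puts into its finite-population step "N = 60 samples from clinic in 3 months". Section 4.8 starts from an average of 2 smears a day, "making 10 in a week and 40 samples in a month".

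**Who counts towards the target.** Section 4.5 requires consent and an age of at least 25. Section 4.7 excludes, among others, women who are menstruating, pregnant, on hormone replacement therapy, or who have vaginitis or overt cervical pathology. The volumes in sections 4.3 and 4.8 are counts of samples or smears. Neither section applies a fraction for eligibility or consent.

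**The concern.** A trial should have one recruitment target, and the accrual forecast should be for that target. Here the section on data collection, which the recruiting staff would work from, carries a smaller number than the sample size section. Its 3-month calendar fits the smaller number.

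Correcting the number alone would not repair the sentence, because 3 months at 40 a month does not reach 132. The second clinic volume, in section 4.3, is half the first, so the reader cannot tell which rate the forecast rests on. At stake are a clear end point for recruitment and a realistic calendar.

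**Working it through.** **Step 1: reproduce 132.** Inputs from section 4.3: proportions 0.01 and 0.005, so P = 0.0075 and E = 0.005; Z values 0.84 and 1.96; N = 60; attrition 10%.

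- n = (0.84 + 1.96)² × 2 × 0.0075 × 0.9925 / 0.005² = 0.116718 / 0.000025 = 4668.72, rounded up to 4669.
- Finite-population step: 4669 / (1 + 4669/60) = 59.24, taken as 60 per arm, 120 in total.
- Attrition: 60 + 6 = 66 per arm, 132 in total.

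The figure of 132 follows from section 4.3. Whether the finite-population step is valid is a separate question and is not judged here.

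**Step 2: look for 102.** Section 4.3 gives 120 before attrition and 132 after it. Dividing by 1 − 0.10 instead of adding 10% gives 60/0.9 = 66.7, so 67 per arm and 134 in total. None of these is 102. In the permuted blocks of 4 of section 4.9, 132 is 33 whole blocks, while 102 is 25.5.

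**Step 3: compare clinic volume with the target.** Every row assumes that each woman screened is eligible and consents. The last row also assumes 21 to 22 weekdays a month, so 63 to 66 in 3 months, before public holidays.

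| Basis | Volume in 3 months | 132 as a share of it | Time for 132 | Time for 102 |
|---|---|---|---|---|
| Section 4.3: 60 per 3 months | 60 | 220% | 6.6 months | 5.1 months |
| Section 4.8: 40 a month | 3 × 40 = 120 | 110% | 132/40 = 3.3 months | 2.55 months |
| Section 4.8: 10 a week, 13 weeks | 130 | 102% | 13.2 weeks | 10.2 weeks |
| Section 4.8: 2 a working day | 126 to 132 | 105% to 100% | 66 working days | 51 working days |

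The 3-month calendar holds for 102 on every section 4.8 basis. For 132 it is met only at the very top of the last row. On the section 4.3 volume neither target is reached in 3 months.

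**Step 4: size of the discrepancy.** 132 − 102 = 30 women, or 23% of the target. Recruitment ending at 102 would mean 102/2 = 51 per arm randomised, against 66 planned and against the 60 that section 4.3 wants before its attrition allowance.

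**Step 5: knock-on in section 4.3.** The clinic volume is also the N of the finite-population step. With N = 120, that step gives 4669 / (1 + 4669/120) = 117 per arm instead of 60. Choosing one rate therefore touches the sample size calculation as well as the calendar.

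**The case against.** Four points can be made for the protocol.

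- **The number already governs.** Section 4.3 is directive and the abstract repeats it, whereas section 4.8 only voices an expectation. A missed forecast costs time and not power. This stands. A reader might infer that the trial plans to stop at 102 women or at 3 months and so gives up power for the pain score, but no section makes either a stopping rule.
- **102 is probably a slip.** It is 120 with two digits exchanged, 120 is the total before attrition, and 3 × 40 is exactly 120. This is plausible but is inference. Even with 120 restored, the sentence would still fall short of the 132 to be recruited.
- **The clinic can do more than 120.** A reader might infer from 40 a month that 132 in 3 months is impossible. The daily and weekly rates do not support that: they give 126 to 132 and 130. What stands is the absence of any margin, because these are counts of all women screened, before consent and the exclusions in section 4.7.
- **The two volumes might be compatible.** The 60 could be meant as one arm's share of 120. The protocol does not say so; section 4.3 presents 60 as the clinic's samples over 3 months and as the study population.

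A calculated loss of power for pain is also tempting. It would need a standard deviation borrowed from another trial, which used a visual analogue scale in gynaecological oncology patients and compared gel with water. It would also be tempting to apply the 10% attrition, yet the score is taken at the same visit, straight after the smear. The protocol makes no power claim for pain, so such a figure would not describe this plan.

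**Conclusion.** The concern holds as an internal contradiction in the target and in the accrual figures. The 102 of section 4.8 is the outlier: section 4.3 and the abstract agree on 132, and nothing yields 102. The clinic volume differs twofold between sections 4.3 and 4.8.

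For the actual target, 3 months is short by about 10% at the stated monthly rate, has no slack on the most favourable count, and is less than half the time needed on the section 4.3 volume. These are minimum times at full uptake. Real uptake is not given in the protocol, so no particular longer duration can be derived from it.

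The 51 per arm is conditional on recruitment actually ending at 102, which the protocol does not plan. Confidence is high for the mismatch of 102 with 132 and of 60 with 120. The protocol does not support a claim that 132 in 3 months is arithmetically impossible, or that a loss of power is built in.

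**What to change.** - In section 4.8, replace 102 by 132.
- State one clinic rate and use it in both sections 4.3 and 4.8. Because that rate is the N in section 4.3, say whether the calculation there is affected (Step 5 of the working) or why 132 is kept.
- State that recruitment ends when 132 women have been randomised, and not at a calendar date.
- Have the investigator restate the expected duration from the reconciled rate and an explicit assumption about the share of screened women who are eligible and consent. A duration should not be written in until both are given.

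The cost is a few sentences and a longer stated calendar. Aligning section 4.8 with the existing target adds no women to the 132 already planned.

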Purposive sampling approach will be employed. Following informed consent, selected women will be assigned at random into two arms, namely the gel group and no gel group with the aid of computer created sporadic numbers. The sequence of randomization will be generated by tfhe computer via randomly permuted blocks (blocks of 4, allocation ratio 1:1). An independent person will perform the randomization and will not be involved in the study. The independent person will create a randomization table using computer software program available at <http://mahmoodsaghaei.tripod.com/Softwares/randalloc.html>. Serially numbered opaque sealed envelopes will be used for allocation concealment. The study interventions would be printed in a sheet of paper put in serially numbered opaque closed envelopes. The envelopes would be kept and opened by an independent person. Once the envelope is opened the allocation of the participant would not be changed. Each of the envelopes will contain either a sheet of paper showing gel group (Group A) placing the patient into the group using the speculum lubrication or a paper displaying no gel group (group B) placing the patient into the group receiving dry speculum (without speculum lubrication). Participants cannot be switched from one group to the other once they are placed in a group.

4.10 **STUDY PROCEDURE**

The consent for Pap smear will be gotten for each person during the visit. After explaining the procedure, the woman will be placed in dorsal position with the legs flexed at the knee and adducted at the hips.

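### Section 4.9 prescribes purposive sampling with no rule for who is selected, so entry is discretionary; the main harm is to whom the results describe

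*Protocol*

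**What the plan says.** Section 4.9 opens with the sampling method, "Purposive sampling approach will be employed", and continues: "Following informed consent, selected women will be assigned at random into two arms". Section 4.4 gives the same order of steps: "An informed consent will be gotten from patients before they are selected to participate in the research". Selection therefore comes after consent. Apart from the inclusion and exclusion criteria in sections 4.6 and 4.7, no rule says which consenting women are selected, and nobody is named as the selector.

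Section 4.5 describes the source population without a selection step: "The women will be recruited from consenting patients who are at least 25years old", presenting to the clinic for a routine smear.

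On allocation, section 4.9 specifies 1:1 randomisation in permuted blocks of 4, generated by an independent person who is not otherwise involved. Serially numbered, opaque, sealed envelopes are kept and opened by an independent person. Sections 4.8 and 4.10 have the researcher and five research assistants collect the data and perform the procedure. Section 4.13 says that they know the assignment.

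On flow, section 4.8 starts from a mean of two smears a day and derives the weekly and monthly totals, "making 10 in a week and 40 samples in a month"; it expects 102 women in three months. Section 4.3 uses a different flow, "N = 60 samples from clinic in 3 months", and sets the total to be recruited at 132.

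**The concern.** Purposive sampling means inclusion by judgement. With no stated basis for the judgement, an eligible woman who has consented may still not be entered, and a reader of the results could not tell why. The aim concerns women having Pap smears at this hospital. Pain score, willingness to return and the unsatisfactory rate can all vary with the kind of woman entered, for example with her expected tolerance of the examination. If entry follows an unrecorded judgement, the results describe the women chosen and not necessarily those who attend.

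A second, smaller issue concerns the comparison of the arms. Discretion over entry is the step through which a guessed allocation can influence who is enrolled. The block size is fixed and disclosed, and the operators see each allocation as it is used, so some later allocations in a block can be inferred.

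**Working it through.** **Sampling text.** Set side by side, section 4.5 takes consenting women aged 25 or over who present for a routine smear, while sections 4.4 and 4.9 add a selection after consent. Either the selection does nothing beyond checking eligibility, in which case purposive is the wrong word, or it does something more, in which case the rule is missing. The proforma in Appendix 2 has an eligibility checklist, but no field for a refusal or for an eligible, consenting woman who was not entered.

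**The plan's own figures, reproduced** (arithmetic only, without endorsing the finite-population step):
- Section 4.3: 4669 / (1 + 4669/60) = 59.2, taken as 60 per arm; 60 + 6 = 66 per arm; 2 × 66 = 132.
- Section 4.8: 2 a day × 5 days = 10 a week; 10 × 4 = 40 a month; 40 × 3 = 120 in three months (10 × 13 = 130 if 13 full weeks are counted).
- Section 4.3: 60 in three months, which is 20 a month.

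**Target against flow, with every woman who has a smear enrolled:**

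| Target | Smears in 3 months | Share needed | Surplus or shortfall | Months needed |
|---|---|---|---|---|
| 132 | 120 | 110% | 12 short | 3.3 |
| 132 | 130 | 101.5% | 2 short | 3.05 |
| 132 | 60 | 220% | 72 short | 6.6 |
| 102 | 120 | 85% | 18 spare | 2.55 |
| 102 | 60 | 170% | 42 short | 5.1 |

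These figures are before any exclusion or refusal. At 102 women and 120 smears, the 18 spare exist only if more than 102/120 = 85% of the women are eligible and consent. If 70% to 90% are eligible and consent (an assumption; the protocol gives no figure), reaching 132 at 40 a month takes 132/(40 × 0.9) = 3.7 to 132/(40 × 0.7) = 4.7 months.

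**Guessing in blocks of 4.** For an observer who knows the block size and every earlier allocation, the chance of a correct guess at positions 1 to 4 is 1/2, 2/3, 2/3 and 1. The mean is (17/6)/4 = 70.8%. If women entered under a gel guess differ on average by d standard deviations from those entered under a no-gel guess, the difference between arms is d × (2 × 0.708 − 1) = 0.417d. The protocol gives no basis for d. The 70.8% is itself an upper value, because six operators share the work and may not know one another's allocations.

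**The case against.** The strongest case against is that purposive may mean only that women who meet the listed criteria are taken. Consent precedes selection, and section 4.5 can be read as recruiting all eligible attenders. Selection before concealed randomisation affects both arms alike. If the target uses up the whole flow, there is also little surplus from which to choose.

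Much of this stands, and it rules out three stronger readings:

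- *Staff hand-pick who is offered the trial.* A reader might infer this because the only study personnel described at the clinic are those who perform the procedure. No section says it. The selector is unnamed, and the discretion that the text leaves lies after consent.
- *The comparison of arms is biased by a known amount.* An independent person generates the sequence, envelopes are opaque, sealed and opened by an independent person, and no switching is allowed. A numerical bias would need an invented value of d and perfect tracking of earlier allocations. Neither is in the protocol.
- *The clinic flow leaves no room to select at all.* That combines the 132 of section 4.3 with the three months of section 4.8, which is an expectation attached to 102 women. No closing date is set, and a longer period restores room to select.

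What does not stand is the benign reading as a full answer. Under it, the named method contradicts the practice in section 4.5, and the wording still permits leaving out eligible, consenting women without a record.

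**Conclusion.** The point holds in a limited form. Section 4.9 names a discretionary sampling method, gives it no criterion beyond eligibility and provides for no record of women not entered. The main consequence is for applicability: it would be unclear which women the pain, willingness and adequacy results represent. Arm-dependent entry is a secondary risk, resting on the fixed blocks of 4 and the operators' knowledge of past allocations, and its size cannot be derived from the documents.

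At 132 women and 40 smears a month there is no surplus to select from within three months (110% of the flow needed, 12 short). This depends on joining the target from one section to the period from another. The conflicts between 132 and 102, and between 60 and 120 smears per three months, are a separate inconsistency in the recruitment plan. A change of sampling method would not cure them.

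**What to change.** In section 4.9, replace purposive sampling with consecutive enrolment: every eligible, consenting woman presenting for a routine smear is entered, in order of arrival. Delete the references to selection after consent in sections 4.4 and 4.9. Add a one-page screening log that counts women approached, women ineligible (with reason) and women declining. The checklist in Appendix 2 already lists several of the exclusion reasons.

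The cost is an edit of a few words and slightly more record keeping by existing staff, at about two women a day.

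Separately, state one recruitment target (132 or 102), one clinic flow (60 or 120 per three months) and a recruitment period that follows from them after allowing for exclusions and refusals.
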